### Trial design

OASIS-D has three different parts. Part one consists of a cross-sectional epidemiological chart review study in which basic historical and clinical characteristics, including past and current presence of suicidality, will be recorded in all consecutively hospitalized patients with MDD (patient population 1 (PP1)). Part two includes a consented subgroup of PP1 with suicidality that even ≥ 48 h post admission still presents with suicidality (eliminating transient, brief suicidality in response to an acute internal or psychosocial stressor) and that consents to undergo in-depth assessments of their past and present psychiatric history, psychiatric diagnoses and psychopathology, including suicidality (PP2). Part 3 includes a subgroup of PP2 whose MDD diagnosis and ongoing suicidality have been confirmed with research interviews and who are followed naturalistically for 6-months, reflecting usual care of adults with MDD and suicidality. Data collection will occur at inpatient admission (T0, epidemiological PP 1), at baseline in patients with ongoing suicidality, i.e. at least 48 h after T0 (T1; PP2 as a subgroup of PP1), and in PP3 (subgroup of PP2) at T1 (more detailed baseline assessments), discharge (T2), 3 months after T1 (T3) and 6 months after T1 (T4) (see Fig. 1). Due to the variability of hospital discharge (T2), the T2 assessment may occur after T3 (3 months) or concurrently with T4 (6 months).

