### Primary inclusion criteria

Inclusion criteria for PP1 are (i) male and female patients; (ii) aged between 18 and 75 years; (iii) admitted to a psychiatric inpatient unit, and (iv) having an ICD-10-based chart diagnosis of single depressive episode (F32) or recurrent depressive episode (F33).

Inclusion criteria for PP2 (originating from PP1) are (i) male and female patients; (ii) aged between 18 and 75 years; (iii) admitted to a psychiatric inpatient unit; (iv) having an ICD-10-based *clinical* diagnosis of a single or recurrent depressive episode of *at least moderate severity*, including single depressive episode, moderate episode (F32.1), single depressive episode, severe episode without psychotic symptoms (F32.2), single depressive episode, severe episode with psychotic symptoms (F32.3), recurrent depressive episode, currently moderate episode (F33.1), recurrent depressive episode, currently severe episode without psychotic symptoms (F33.2), and recurrent depressive episode, currently severe episode with psychotic symptoms (F33.3); (v) *clinically* diagnosed suicidality that persists for ≥ 48 h after inpatient admission; and (vi) sufficient German language skills to understand the purpose and procedures of the study and cooperate with the study procedures; and (vii) providing written informed consent to participate in the study.

Inclusion criteria for PP3 (originating from PP2) are (i) male and female patients; (ii) aged between 18 and 75 years; (iii) admitted to a psychiatric inpatient unit; (iv) having an ICD-10-based *research* diagnosis according to the Mini-International Neuropsychiatric Interview (M.I.N.I.) [71] of a single or recurrent depressive episode of *at least moderate severity* (for details, see PP2 above); (v) *research interview-based* suicidality with a score ≥ 1 on item 2 (passive suicidality) OR item 3 (active suicidality) using the Sheehan–Suicidality Tracking Scale (S-STS) [21]; (vi) written informed consent to participate in the study.

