Hypothesis 3A: We hypothesize that the time to remission of suicidal symptoms after the baseline is a major determinant of shorter overall duration of passive or active suicidal ideation (PASI) during the entire 6-month observation period.

Hypothesis 3B: We hypothesize that the rate of remission of suicidal symptoms after baseline is a major determinant of lower recurrence of PASI during the 6-month observation period.

Hypothesis 3C and 3D: We hypothesize that a longer total duration of PASI (Hypothesis 3C) and a greater risk of recurrence of PASI after complete remission (Hypothesis 3D) during the 6-month observational phase is associated with the following factors at time T0 (i.e., “moderators”): greater severity of (i) depressive symptoms [28, 36, 42, 43], (ii) manic symptoms (below the threshold of (hypo)mania as part of MDD), (iii) anxiety symptoms [28, 36, 45], (iv) anger and hostility [43], (v) quality of life impairment [48, 49], (vi) global symptoms of illness and (vii) suicidality [28, 36, 42, 47], (viii) higher number of lifetime depressive episodes, (viii) index admission as part of a psychiatric emergency, (ix) longer duration of current depressive episode [44], (x) higher non-adherence to pharmacological and non-pharmacological treatments, (xi) comorbid borderline personality disorder [35, 46], and (xii) comorbid substance use diagnosis [28].

Exploratory study aim 1 of PP3 is to describe the association between PASI and suicide attempts (S-STS item 14) as well as with the utilization of outpatient and inpatient care services during the 6-month observation period.

Exploratory hypothesis 1A, 1B and 1C: We hypothesize that a higher number of days with PASI (exploratory hypothesis 1A), a higher number of days with active suicidal ideation (exploratory hypothesis 1B) and a higher number of suicide attempts (exploratory hypothesis 1C) during the 6-month observation period are significantly associated with a higher number of (i) outpatient appointments, (ii) emergency department visits, (iii) inpatient hospitalizations, (iv) hospitalizations as part of psychiatric emergencies, (v) psychiatric hospital bed days, and (vi) suicide-related hospital bed days.

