Hypotheses 3A and 3C will be analyzed by means of methods for count data, such as Poisson or Negative Binomial models, depending on whether overdispersion is present in the data or not. The dependent variable will be overall duration of PASI during the 6-month observation period and the independent variable of main interest will be time to remission of suicidal symptoms after baseline.

Hypotheses 3B and 3D will be analyzed by using Cox proportional hazard models, where the dependent variable will be time-to-first-recurrence of PASI and the independent variable of main interest will be time to remission of suicidal symptoms after baseline.

Further independent variables for regression analysis will include patient, illness, and treatment variables, including severity of depressive symptoms (MADRS, Quality of Life in Depression Scale (QIDS-S) [79]), manic symptoms (YMRS), anxiety (BAI), anger/hostility (STAXI, AF-BP), global illness symptoms (CGI-S), quality of life (EQ-5-DL), and suicidality (S-STS); presence of psychiatric emergencies; number of lifetime depressive episodes; duration of current depressive episode; nonadherence to pharmacological and nonpharmacological treatments; and comorbid borderline personality and substance abuse. Additionally, a random factor accounting for clustering of patients in centers will be added to the models.

Assuming a minimum requirement of 10 patients per predictor variable in regression analyses [91–93] and approximately 20 independent patient, illness, and treatment variables that would be tested as potential correlates of time to remission of suicidality, we estimated that a sample size of at least 200 would be required.

Additionally, as a secondary analysis, we will divide patients into two groups using the median time up to the first S-STS value of zero, which are either below or above the median time to first complete remission of suicidality.

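### Hypothesis 3A regresses total PASI duration on time to remission, which overlaps that total, so a significant result is nearly guaranteed and cannot show that faster remission predicts a better later course

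*Protocol article*

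**What the plan says.** In the Protocol article, Aims and hypotheses, Hypothesis 3A states that "time to remission of suicidal symptoms after the baseline is a major determinant of shorter overall duration" of PASI, counted over the whole 6 months from T1.

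Sample size and statistical analyses turns this into a model. Hypotheses 3A and 3C share one specification, using "methods for count data, such as Poisson or Negative Binomial models, depending on whether overdispersion is present in the data or not". For both, the text gives the outcome as "overall duration of PASI during the 6-month observation period and the independent variable of main interest will be time to remission". Baseline patient, illness and treatment variables and a random factor for centre are added. No offset, landmark or restriction to the period after remission is stated.

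Three other statements matter:
- Primary inclusion criteria: PP3 entry requires an S-STS "score ≥ 1 on item 2 (passive suicidality) OR item 3 (active suicidality"), so PASI is present when the clock starts.
- The only working description of remission is in the secondary analysis, which splits patients "using the median time up to the first S-STS value of zero".
- Trial design: assessments after discharge are "3 months after T1 (T3) and 6 months after T1 (T4").

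Hypotheses 3B and 3D are analysed separately, with Cox models for time to first recurrence. The article describes its p-values and confidence intervals as hypothesis-generating, without multiplicity adjustment.

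**The concern.** The predictor overlaps the outcome. Time to remission covers the first stretch of follow-up, when the patient is by definition not yet remitted, and the PASI days in that stretch are part of the total being explained. A late remitter accumulates a larger total simply by remitting late. A positive coefficient then appears even if, once remitted, early and late remitters fare exactly alike.

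3A is the first hypothesis under the primary aim of PP3. If its test is positive under almost any plausible course, the analysis could support calling speed of remission a major determinant of outcome without having examined whether it predicts anything beyond itself.

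The shared specification also affects 3C. That hypothesis asks which baseline factors go with longer total PASI. With time to remission in the model, a factor that lengthens PASI by delaying remission loses its effect to the adjustment.

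**Working it through.** **The plan's own figures.** 260 × 0.80 = 208 and 315 × 0.66 = 207.9, so 208 patients with month-6 data is reproduced. The minimum is 10 × 20 = 200. The article gives no effect size or power for 3A, so there is no stated figure for the test itself.

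**Inputs.** From the article: n = 208, two-sided alpha 0.05, 6 months from T1 (182 days used), PASI present at T1. Assumed, because the article gives no values: median time to remission R of 14, 30 or 60 days (exponential, capped at 182); share g of post-remission days with PASI, mean 0.05 to 0.5, varying between patients; share f of pre-remission days with PASI, 0.2 to 1. Covariates, the centre factor and dropout were not simulated.

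**Algebra.** With no carry-over, expected total PASI days are

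D = fR + g(182 − R) = 182g + (f − g)R.

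The slope on R is f − g. It is zero only if PASI is as dense before remission as after.

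Example with f = 1, g = 0.2: R = 14 gives 14 + 0.2 × 168 = 47.6 days; R = 60 gives 60 + 0.2 × 122 = 84.4 days. The difference of 36.8 days is 0.8 × 46, although both patients have the same PASI share after remission. With f = 0.3, g = 0.2 the totals are 37.8 and 42.4 days.

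**Planned outcome, no carry-over, f = 1** (negative binomial, 200 runs each). Cells show the percentage of runs significant in the positive direction, then the rate ratio per 30 days.

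| Median R | g = 0.05 | g = 0.1 | g = 0.2 | g = 0.3 | g = 0.5 |
|---|---|---|---|---|---|
| 14 d | 100; 2.37 | 100; 1.84 | 100; 1.47 | 98.5; 1.30 | 76.5; 1.15 |
| 30 d | 100; 1.68 | 100; 1.51 | 100; 1.34 | 100; 1.24 | 100; 1.13 |
| 60 d | 100; 1.46 | 100; 1.38 | 100; 1.28 | 100; 1.21 | 100; 1.12 |

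The correlation between R and D ran from 0.21 to 0.97.

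**Intermittent PASI before remission** (median R 30 days): f = 0.7, g = 0.2 gives 100%; f = 0.5, g = 0.2 gives 97.5%; f = 0.3, g = 0.2 gives 19.5%; f = 0.5, g = 0.4 gives 13%; f = g = 0.2 gives 2%.

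**Can the test tell the possible truths apart?** Poisson with robust standard errors, 1000 runs each, median R 30 days, f = 1, g = 0.2. Carry-over is the change in log-odds of a post-remission PASI day per 30 days of later remission.

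| Carry-over | Total duration: significant; rate ratio | Post-remission days with offset: significant; rate ratio |
|---|---|---|
| −0.4 (late remitters do better) | 100%; 1.25 | 95.2%; 0.71 |
| −0.2 | 100%; 1.28 | 46.3%; 0.85 |
| 0 | 100%; 1.30 | 5.0%; 1.00 |
| +0.2 | 100%; 1.33 | 63.6%; 1.17 |
| +0.4 (late remitters do worse) | 100%; 1.35 | 99.5%; 1.33 |

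The planned test is positive in every row, including those where later remission is followed by fewer PASI days. With no carry-over and g from 0.1 to 0.5, the post-remission analysis rejected in 4.8-5.8% of runs. Some negative binomial fits gave convergence warnings and ran conservative for the post-remission outcome (0.5-4.5% for f = 1), so the robust Poisson runs are the better guide to test size.

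**3C.** A standardised moderator acting only through R (R multiplied by exp(0.5x); median R 30 days, g = 0.2) was detected in 99.0% of runs without R in the model and in 5.6% with it.

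**The case against.** Several arguments on the other side have weight.

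- *It is not an identity.* A reader might infer that total duration equals time to remission plus later PASI days, so that 3A must come out positive whatever the truth. The article does not support that. Remission is described as an S-STS of zero, which is stricter than absence of PASI on items 2 and 3, so days before remission can be free of PASI. The result depends on f − g and disappears when the two are equal. This stands.
- *3A asks about the total.* A reader might also infer that the analysis says nothing about the study's question. That goes too far. Duration of suicidality is an aim in itself, and how much of the total is accounted for by time to first remission is useful description. This stands for the size of the association, not for a test against zero.
- *The later course is covered by 3B and 3D.* Their outcome is not a total containing the predictor, so this stands. It does not repair the 3A test.
- *The study is exploratory.* Labelling p-values hypothesis-generating tempers multiplicity claims; it does not make a nearly predetermined p-value informative.
- *The percentages rest on assumptions and omit covariates and centre.* True, which is why a range is shown. Adjusting for baseline covariates does not remove the overlap.
- *Patients who never remit.* How they are coded can be left to the full protocol or analysis plan and is not counted here.

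**Conclusion.** The concern holds for the 3A test. Both variables are fixed in the article, they overlap, and nothing stated separates them. With continuous PASI before remission and no carry-over, a significant positive result appears in 98.5-100% of runs for post-remission shares of 0.05-0.3, and in 76.5-100% at 0.5, with rate ratios of 1.12-2.37 per 30 days that owe nothing to any effect of early remission on the later course. The result weakens materially only when PASI before remission is nearly as sparse as after it, which sits poorly with a sample selected for PASI that has persisted at least 48 hours.

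The conclusion is limited to this: a significant 3A result is nearly guaranteed and cannot be read as evidence that faster remission leads to a better later course. It is not certain by construction, and the magnitude of the association remains descriptive information. The simulation assumes the stated shares and remission times, complete 182-day follow-up and exactly known remission days. The same specification, applied to 3C, would hide moderators that work by delaying remission. The sample-size figures reproduce and are unaffected.

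**What to change.** 1. For the 3A test, take PASI days after first remission as the outcome, with log(remaining observed days) as offset, among remitters with follow-up left after remission. Patients first remitting at the last assessment have no remaining days and must be excluded explicitly, because the offset is undefined for them.
2. Alternatively, use a month-3 landmark: remitted by month 3 (yes/no) predicting PASI days from month 3 to month 6. This removes the overlap in time, but days before remission in patients who remit after month 3 still count, so it answers a prognostic question; the 4.8-5.8% rejection rate above was obtained for option 1 only. It also needs a rule for patients whose T3 is not held because it falls within two weeks of discharge.
3. Report the association between time to remission and total PASI duration descriptively, without a test against zero, and report the proportion who never remit.
4. Keep total PASI duration as the 3C outcome, but leave time to remission out of that model.

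The cost is in wording and analysis; no new data are needed. The 3A test would apply to a subset. With 208 patients projected at month 6 and a stated minimum of 200, losing more than 208 − 200 = 8 takes option 1 below the plan's own minimum. The estimate will be less precise, and the question moves closer to that of 3B.

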Regarding PP2, based on clinical experience and questionnaire information from the recruitment centers as part of the design preparations, an estimated 33% of 3331 patients (*n* = 1,099) with a clinical diagnosis of at least moderately severe MDD are assumed to be still suicidal ≥ 48 h after admission. Approximately 60% of this group are expected to consent to participate in the interview-based study (and the naturalistic, 6-month follow-up study, should they also fulfill criteria for PP3, determined during participation in PP2). The following analyses of congruence between clinical diagnosis and research diagnosis (gold standard) of at least moderately severe MDD will take place:(a) two groups will be formed (primary analysis), i.e., positive vs. negative validation of the clinical diagnosis with the research-based interview M.I.N.I.,(b) use of descriptive statistics to estimate proportions of patients meeting the gold standard of research diagnosis and their confidence intervals (see a, hypothesis 2A), as defined by diagnostic concordance with the clinical diagnosis at the time of hospitalization; and.(c) to perform multiple mixed logistic regression analysis with backward elimination to compare patients with positively validated and non-validated at least moderately severe MDD (see a, hypothesis 2B), with random factors to account for clustering of patients in centers.

Regarding PP3, the OASIS-D study was initiated with the assumption that approximately 50% of the 520 patients surveyed in PP2 would not meet ICD-10 criteria for the inclusion criteria of at least moderately severe MDD, so that260 patients would be enrolled in PP3. Assuming a 20% drop out rate, this would yield n = 208 with data at 6 months. During the interim analysis 2, in September 2022, we noted a higher drop-out rate of 34% in PP3 than the 20% expected attrition rate at the time of the study design. Due to this finding, the number of patients in PP3 was increased to n = 315, so that with an attrition rate of 34%, the number of patients with data at month 6 would remain at n = 208. Since there was a higher than initially projected transition rate from PP2 to PP3, so that the n of patients entering PP2 did not need to be increased.

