Furthermore, comparisons between the slower and faster remitting group of continuous variables will be performed using multiple comparison procedures (MCPs) with 3 measurement time points (T1, T2, and T4). Because only the primary outcome and very limited other parameters are collected by telephone at T3, data at T3 are not included in these analyses. Because the timing at T2 (hospital discharge) is variable, and this timing is not independent of the outcome measured, the duration between T1 and T2 is included as a covariate in the analyses. Cross-group comparisons of dichotomized or categorical variables are performed using chi-square statistics. For ease of comparison, continuous outcomes, such as depressive symptoms and medication use are calculated. All analyses are two-sided, with alpha = 0.05. Due to the exploratory nature of the study, no adjustment for multiplicity between different endpoints is conducted. Hence, p-values and confidence intervals need to be interpreted in a hypothesis-generating manner. In addition, multivariable regression analysis with backward selection will be performed to identify independent moderators or mediators of continuous and categorical outcomes, respectively. Moreover, missing continuous data will be treated using multiple imputation using chained equations and random effects for the clustering of patients in different centers.

Among the exploratory objectives, the patient, illness, and treatment factors that influence the risk of different levels of active suicidality are identified: i) active suicidality (S-STS item 3), ii) active suicidality with preparatory action (S-STS item 12), iii) self-injurious behavior without suicidal intent (S-STS item 13), and iv) suicide attempt (S-STS item 14) during the observation period of inpatient treatment and within 6 months of study inclusion (T1). Target parameters i)-iv) are associated with slower initial resolution of suicidality (lower than median time to S-STS score = 0); and with: Depressive symptom severity (MADRS, QIDS-S), manic symptoms (YMRS), anxiety (BAI), anger/hostility (STAXI, AF-BP), and global illness symptoms (CGI-S); higher number of lifetime depressive episodes; more frequent psychiatric emergencies; longer duration of current depressive episode; non-adherence to pharmacological and non-pharmacological treatments; comorbid borderline personality; and substance abuse diagnoses.

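### The PP3 sample size counts patients per predictor, but the Cox models for 3B and 3D depend on recurrences, and the outcome named in the rationale is the main independent variable in the 3A–3D models

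*Protocol article*

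**What the plan says.** All of the following is in the Protocol article, Sample size and statistical analyses, unless stated otherwise.

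- **Sizing rule.** "Assuming a minimum requirement of 10 patients per predictor variable in regression analyses", applied to "approximately 20 independent patient, illness, and treatment variables that would be tested as potential correlates of time to remission of suicidality", leads to "we estimated that a sample size of at least 200 would be required".
- **Enrolment.** After higher drop-out than planned, "the number of patients in PP3 was increased to n = 315". At the observed 34% attrition this keeps 208 patients with month-6 data, the same number as in the original plan.
- **Models.** 3A and 3C use Poisson or negative binomial models for the total duration of passive or active suicidal ideation (PASI). "Hypotheses 3B and 3D will be analyzed by using Cox proportional hazard models", with time to first recurrence of PASI as the dependent variable. In both pairs, time to remission is the independent variable of main interest.
- **Who can recur.** Under Aims and hypotheses, 3D defines recurrence as following complete remission.
- **Other analyses.** In a later paragraph, "multivariable regression analysis with backward selection will be performed to identify independent moderators or mediators"; the outcomes are described only as continuous and categorical and are not listed. The exploratory objectives look for factors influencing S-STS items 3, 12, 13 and 14.
- **Status.** No multiplicity adjustment is made, and results are to be read as hypothesis-generating.

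**The concern.** A rule of ten per predictor counts whatever carries the information in the model. In a regression of a continuous or count outcome observed in every patient, the patient is a reasonable unit. In a Cox model it is the event, and a patient who never remits cannot have a recurrence. The rule is stated for regression analyses in general, and enrolment was raised to protect the resulting figure. A reader will therefore take about 200 patients as enough for some 20 predictors in each PP3 regression. For 3B and 3D that does not follow.

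The rationale also does not match the models it is meant to support. It sizes for correlates of time to remission, while the 3A–3D models have PASI duration and time to first recurrence as outcomes.

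At stake is the reliability of the moderators reported for recurrence. With few events per predictor, coefficients are unstable and tend to be exaggerated, and intervals computed after any data-driven selection are too narrow. Primary objective 3 explicitly seeks significant moderators and mediators.

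**Working it through.** **1. The plan's own figures reproduce.**
- Rule: 10 × 20 = 200.
- Original plan: 520 × 0.50 = 260 enrolled; 260 × 0.80 = 208 with month-6 data.
- Revised plan: 315 × 0.66 = 207.9, i.e. 208. (Working back, 208 / 0.66 = 315.2, which rounds up to 316; the difference of one patient is immaterial.)

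The arithmetic is sound. The question is the unit.

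**2. The same rule in events, for 3B and 3D.** Needed events = 10 × number of predictors, with each variable counted as one parameter. The base lies between 208 (month-6 data) and 315 (all enrolled, since a Cox model uses events observed before drop-out).

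The variables named are MADRS, QIDS-S, YMRS, BAI, STAXI, AF-BP, CGI-S, EQ-5-DL, S-STS, psychiatric emergencies, lifetime episodes, episode duration, two kinds of non-adherence, borderline personality and substance abuse. That makes 16, or 17 with time to remission.

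| Predictors | Events needed | Share of 208 | Share of 315 |
|---|---|---|---|
| 20 (plan's figure) | 200 | 96% | 63% |
| 17 | 170 | 82% | 54% |
| 16 | 160 | 77% | 51% |

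These are shares of patients who must first remit completely and then recur within six months. With an assumed 90% remitting, 208 × 0.90 = 187 patients could recur at all, fewer than the 200 needed. On the base of 315, 315 × 0.90 = 283.5 remit, and 200 / 283.5 = 71% of them would have to recur.

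**3. Expected events under assumed rates.** The document gives none, so these are assumptions: 70–90% remit, and 20–50% of remitters recur. Events = n × P(remit) × P(recur given remission).
- n = 208, low: 208 × 0.70 × 0.20 = 29; 29 / 20 = 1.5 per predictor.
- n = 208, high: 208 × 0.90 × 0.50 = 94; 94 / 20 = 4.7 per predictor.
- n = 315, low: 315 × 0.70 × 0.20 = 44; 44 / 20 = 2.2 per predictor.
- n = 315, high: 315 × 0.90 × 0.50 = 142; 142 / 20 = 7.1 per predictor.

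At ten events each, that supports about 2 to 9 predictors (n = 208) or 4 to 14 (n = 315). A wider assumed range, 50–90% remitting and 20–70% recurring, gives 21–131 events at n = 208 and 32–198 at n = 315 (1.0–6.6 and 1.6–9.9 per predictor).

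**4. If an S-STS item is modelled as binary.** The limiting count is the smaller of events and non-events.
- For a perfectly balanced outcome and the 14 factors of exploratory hypothesis 2: 104 / 14 = 7.4 at n = 208, and 157 / 14 = 11.2 at n = 315.
- For suicide attempts at an assumed 5–15%: from 208 × 0.05 = 10 events (10.4 / 14 = 0.7 per predictor) to 315 × 0.15 = 47 events (47.25 / 14 = 3.4).

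**5. Outcome named in the rationale.** It speaks of variables "tested as potential correlates of time to remission of suicidality, we estimated that a sample size of at least 200". In the paragraphs on 3A/3C and 3B/3D, time to remission stands on the other side of the equation. Its further use is a secondary median split into faster and slower remitters, compared by multiple comparison procedures and chi-square tests.

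**The case against.** The strongest defence is that the plan never states that 200 patients suffice for a 20-predictor model of recurrence or of suicide attempts. It ties the figure to time to remission, for which every PP3 patient is at risk from T1. It cites references for its rule, declares itself exploratory, and may leave event counts to a fuller document. The 96% figure is also the least favourable base, because events before drop-out count.

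Part of this stands. The consequence is limited by the exploratory status, and the range from 208 to 315 must be shown. But the sizing paragraph offers no other basis for 3B and 3D, and the outcome it names is not the one those models analyse. This is a stated rationale that does not fit the models, not a missing detail.

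Some stronger readings a reader might infer are not supported:

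- *That backward selection is planned for the Cox models.* The text attaches it to continuous and categorical outcomes; the Cox paragraph names no selection method.
- *That the S-STS items are certain to be under-powered binary models.* No model or dichotomisation is stated, exploratory hypothesis 1C treats attempts as a number, and a balanced item with 14 factors could exceed ten per predictor at n = 315.
- *That time to remission is analysed nowhere as an outcome.* The unspecified categorical outcomes could include slow versus fast remission, although the text does not say so.
- *That PP3 must be enlarged.* Nothing here requires it.

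**Conclusion.** The point holds for 3B and 3D. Ten patients per predictor is the wrong unit for a Cox model of first recurrence. By the plan's own standard, 20 predictors would need 63% to 96% of patients both to remit and to recur, depending on whether all 315 or only 208 contribute; the 16 to 17 named variables would need 51% to 82%. Those thresholds follow from the document alone. The size of any shortfall depends on remission and recurrence rates that the document does not give; under the main assumed ranges it is 1.5 to 7.1 events per predictor instead of 10.

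The count models (3A, 3C) are not affected. For exploratory S-STS outcomes the same limit applies only if they are modelled as binary, and it matters most for rare ones such as attempts. Naming time to remission as the outcome contradicts its role in the 3A–3D models. The practical consequence is unstable, overfitted predictor sets in a hypothesis-generating study; no confirmatory test or power claim fails.

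**What to change.** 1. Restate the rationale: about 200 patients meets the ten-per-predictor rule for the count models (3A, 3C) only. Replace time to remission with the outcomes those models analyse.
2. For 3B, 3D and any binary outcome, state the expected number of events with a range and the assumed remission, recurrence or event rates behind it, on both the 208 and the 315 base.
3. For these outcomes, either limit the prespecified predictors to what the expected events support, or fit the full prespecified set with penalisation (for example ridge, or Firth for a rare binary outcome such as attempts).
4. Say which outcomes the backward selection covers. Where it would be applied to these outcomes, do not run it on the full set.

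The cost is a rewritten paragraph and a change in how some models are fitted, with no extra patients, visits or data. The downside is a less favourable statement of adequacy for 3B and 3D, and fewer or shrunken predictors in those models.
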